### ***Secondary endpoints and safety outcomes***

#### ***Binary outcomes***

Binary efficacy and safety outcomes will be analysed as described for the primary endpoint.

#### ***Shift outcomes***

The median of the absolute values the 95% confidence interval (95%CI) will be calculated using the Hodges-Lehmann methods (i.e. median of all cross differences between treatments based on the Mann-Whitney distribution).

#### *Continuous outcomes*

Continuous variables will be analysed using Mixed Models, including in the model the baseline measurement, the stratification variables, treatment as well as the interaction between treatment and time, declaring time as categorical. The variance-covariance matrix will be fixed initially as unstructured. Contrasts between study groups will be performed by time-point. The treatment effect will be estimated through adjusted means –Least Square Means (LSMeans) – its standard error – Standard Error of Mean (SEM)- and its 95%CI. Differences between treatments will be estimated through the differences between LSMs, SEM and 95%CI.

#### *Survival endpoints*

The survival function as well as the median [95% confidence interval -95%CI-] time to event will be estimated by means of the Kaplan-Meier method. Group comparisons will be done using the (stratified) log-rank test and the (stratified) hazard ratios -HR- (95%CI) were taken from the Cox model.

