| Duration of study              | The observation period will be from randomization until 28 days after randomisation, hospital discharge, ICU admission or death, whichever occurs first.                                                                                                                                                                                                                                                                                                                                                                                                                                                                                                                                                                                                                                                                                                                                                                                                                                                                                                                                                                                                                                                     |
| General design and methodology | 
A multi-center, randomized, clinical trial with two arms to study the efficacy and safety of early treatment with sarilumab plus SOC compared to standard of care (SOC) in patients with COVID-19 pneumonia (BCRSS score 1).
 
Experimental arm: Sarilumab + methylprednisolone (or equivalent doses) plus SOC for COVID-19
 
Control arm: Methylprednisolone (or equivalent doses) plus SOC for COVID-19.
 
Randomization will be 1:1 to any of the treatment groups and will be stratified per center.
 
Methylprednisolone 1mg/kg/day (or corticosteroid dose equivalents) for at least 3 days.
 
SOC includes any drugs that are being used in clinical practice (e.g. lopinavir/ritonavir; hydroxy/chloroquine, and other than those used as part of another clinical trial) according to each site local protocol.
 
Patients will be followed up to four weeks after randomization.
 
Patients randomized to the control arm (CS + SOC group without sarilumab) progressing to severe respiratory failure fulfilling criteria for treatment with anti-IL6 inhibitors according to clinical practice guidelines, as defined by the presence of Brescia-COVID
 |

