| Secondary measures and endpoints | 
Time to progression to severe respiratory failure (Brescia-COVID <math>\geq 2</math>)
 
Time to reduction of supplemental oxygen requirements
 
Time to non-invasive or invasive mechanical ventilation.
 
Rate of hospital discharge and duration of hospitalization
 
Mortality rate and survival time
 
Rate of ICU admission
 
Proportion of patients with at least 1 point progression in the 7-point ordinal scale
 
Ordinal scale:
 
 
1) Not hospitalized, no limitations on activities.
 
2) Not hospitalized, limitation on activities.
 
3) Hospitalized, not requiring supplemental oxygen.
 
4) Hospitalized, requiring supplemental oxygen.
 
5) Hospitalized, on non-invasive ventilation or high flow oxygen devices or oxygen mask with reservoir bag.
 
6) Hospitalized, on invasive mechanical ventilation or ECMO.
 
7) Death.
 
 
Changes from baseline to day 15th in serum levels of inflammatory cytokines.
 
Proportion of patients showing more than >1 organ failure, e.g. cardiovascular, liver and kidney failure
 
Safety and tolerability – Adverse events
 |

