| 
 
• Clinical Severity: progression to severe respiratory failure/ICU admission or death
 
                                                                                                                                                                                                                                                                                                                | 
Time to respiratory failure
Rate of ICU admission
Rate of mortality
                                                                                                                                                                                                                                                                                                                                                                                                                                                                                                                                                                                                                                                                                                                                 |
| 
 
• Oxygenation: 
 
○ Oxygenation free days in the first 15 days
 
○ Incidence and duration of new oxygen use during the study
 
○ Mechanical Ventilation 
 
• Ventilator free days in the 15 days.
 
• Incidence and duration of new mechanical ventilation use during the study
 
 
 
 
 
 | 
Time to reduction of supplemental oxygen requirements
Time to non-invasive or invasive ventilation.
 
Proportion of patients with at least 1 point progression in the 7-point ordinal scale from baseline up to day 15
Ordinal scale:
 
 
1) Not hospitalized, no limitations on activities.
 
2) Not hospitalized, limitation on activities.
 
3) Hospitalized, not requiring supplemental oxygen.
 
4) Hospitalized, requiring supplemental oxygen.
 
5) Hospitalized, on non-invasive ventilation or high flow oxygen devices or oxygen mask with reservoir bag.
 
6) Hospitalized, on invasive mechanical ventilation or ECMO.
 
7) Death.
 
 |

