### *Secondary endpoints*

1. Time to progression to severe respiratory failure
2. Time to reduction of supplemental oxygen requirements
3. Time to non-invasive or invasive ventilation.
4. Proportion of patients with at least 1 point progression in the 7-point ordinal scale from randomization up to day 15

Ordinal scale:

1. Not hospitalized, no limitations on activities.
  2. Not hospitalized, limitation on activities.
  3. Hospitalized, not requiring supplemental oxygen.
  4. Hospitalized, requiring supplemental oxygen.
  5. Hospitalized, on non-invasive ventilation or high flow oxygen devices or oxygen mask with reservoir bag.
  6. Hospitalized, on invasive mechanical ventilation or ECMO.
  7. Death.
5. Rate of hospital discharge
  6. Duration of hospitalization
  7. Mortality rate and survival time.
  8. Rate of ICU admission
  9. Changes in serum levels of inflammatory cytokines.
  10. Proportion of patients showing more than >1 organ failure, e.g. cardiovascular, liver and kidney failure
  11. Safety and tolerability – Adverse event: The occurrence of treatment adverse events (AEs), serious AEs (SAEs), and laboratory abnormalities in the following, but not limited to, parameters: acute phase reactants CRP and ESR, complete blood count (including ANC and platelets), liver enzymes (ALT, AST and AP), and lipid levels, (time frame: up to day 15)

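### Time to reduction of supplemental oxygen is left to plain Kaplan-Meier, log-rank and Cox although death precludes the event; by default deaths are censored and recovery is overstated

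*Protocol*

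**What the plan says.** Section 10, Survival endpoints, gives one set of methods. The survival function and the median "time to event will be estimated by means of the Kaplan-Meier method". For the arms, "Group comparisons will be done using the (stratified) log-rank test and the (stratified) hazard ratios" come from a Cox model. It states no competing-event method and no censoring rule for death, and it does not list which endpoints it covers.

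Section 8, Secondary endpoints, lists "Time to reduction of supplemental oxygen requirements". This is a time-to-event variable, and none of the other methods in section 10 (binary, shift, continuous, remaining variables) is made for one.

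The synopsis, under duration of study, runs observation from randomisation to day 28, "hospital discharge, ICU admission or death, whichever occurs first".

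The missing-data rule in section 10 counts missing binary outcomes as failures. It gives no rule for time-to-event outcomes.

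Hospital stay appears as "Rate of hospital discharge" and, separately, "Duration of hospitalization". The synopsis joins the two as "Rate of hospital discharge and duration of hospitalization". No time to discharge is named, and section 10 does not say which method applies to the duration.

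**The concern.** Kaplan-Meier assumes that a censored patient could still have the event later, at the same rate as those who remain under observation. That suits a patient whose follow-up simply ends. It does not suit a patient who has died, because death rules out any later reduction in oxygen. If deaths are censored at the time of death, one minus Kaplan-Meier estimates recovery in a hypothetical population in which nobody dies.

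Two things follow for this endpoint. The reported probability of recovery is too high and the reported median too short, more so in an arm with more deaths. And if the arms differ in mortality but not in the recovery rate among patients still alive and unrecovered, the curves and the log-rank test show no difference, although fewer patients actually recover in one arm. A reader who takes the curve as the proportion of patients who came down on oxygen would be misled.

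**Working it through.** **The plan's own figure.** The only planning calculation is for the primary binary endpoint: 25% v 10%, two-sided 5%, 80% power. With mean proportion 0.175,

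n = [1.960·√(2·0.175·0.825) + 0.842·√(0.25·0.75 + 0.10·0.90)]² / 0.15² = (1.053 + 0.443)² / 0.0225 ≈ 99.5, so 100 per arm.

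This reproduces the stated 100 + 100 (power 80.2% at 100 per arm). It does not bear on the present point beyond fixing the arm size.

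**Inputs for the check.** The protocol gives no recovery rate and no separate death rate, so both are assumed:
- constant cause-specific hazards, *a* for oxygen reduction and *b* for death;
- a Kaplan-Meier median of 10 days in both arms, so *a* = ln 2 / 10 = 0.0693 per day;
- cumulative death before recovery from 5% to 25%, from which *b* is solved. Death is a component of the primary composite, so under the planning rates deaths within that endpoint's window cannot exceed 25% in the control arm or 10% in the sarilumab arm. The top of the range is therefore extreme.

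**Formulas at day T.**
- One minus Kaplan-Meier, deaths censored: 1 − exp(−aT). This does not depend on *b*.
- Cumulative incidence of recovery: [a/(a+b)]·[1 − exp(−(a+b)T)].
- Cumulative incidence of death: [b/(a+b)]·[1 − exp(−(a+b)T)].
- Day by which half of all patients have recovered: −ln(1 − 0.5(a+b)/a) / (a+b).

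**Day 28.** One minus Kaplan-Meier is 1 − exp(−1.941) = 85.6% in every row. Overstatements are taken before rounding.

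| Deaths by day 28 | b per day | Cumulative incidence of recovery | Overstatement (points) | Half recovered by day (Kaplan-Meier: 10) |
|---|---|---|---|---|
| 5% | 0.0042 | 82.2% | 3.4 | 10.3 |
| 10% | 0.0088 | 78.8% | 6.9 | 10.6 |
| 15% | 0.0138 | 75.2% | 10.4 | 11.0 |
| 20% | 0.0193 | 71.6% | 14.0 | 11.5 |
| 25% | 0.0255 | 68.0% | 17.7 | 12.1 |

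**Day 15.** With the same 5% to 25% range reached by day 15, one minus Kaplan-Meier is 64.6% and cumulative incidence runs from 62.5% to 53.3%. The overstatement is 2.2 to 11.4 points.

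**Comparison of arms.** In 4,000 simulated trials per row, 100 per arm, the recovery hazard was equal in both arms and only deaths differed. The log-rank test (two-sided 5%, unstratified) was run once with deaths censored at death and once with deaths kept at risk to day 28 as not recovered.

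| Deaths | Cumulative incidence, day 28 | Rejects, deaths censored | Rejects, deaths kept at risk |
|---|---|---|---|
| 10% v 10% | 78.8% v 78.8% | 5.9% | 5.2% |
| 10% v 20% | 78.8% v 71.6% | 5.3% | 15.3% |
| 5% v 15% | 82.2% v 75.2% | 4.8% | 14.7% |
| 5% v 20% | 82.2% v 71.6% | 5.0% | 27.0% |

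The Monte Carlo standard error is about 0.3 points near 5% and 0.6 to 0.7 points at 15% to 27%. With deaths censored the test stays close to its nominal level, and both arms have the same expected Kaplan-Meier recovery of 85.6%, although the true proportions recovering differ by about 7 to 11 points.

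**The case against.** The strongest reply is that no sentence says deaths are censored at death. Section 10 calls itself a summary and promises a detailed SAP, and keeping deaths at risk to day 28 can be run with the very methods named. This stands in part: the censoring is a default consequence, not a written rule, and a reader who infers that the protocol orders it goes too far. It does not remove the point. The protocol has already chosen estimator, test and model, it ends observation at death, and an SAP that simply follows it would censor.

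A second reply is that, with deaths censored, log-rank and Cox still validly compare cause-specific recovery rates. That is correct, and the near-nominal rejection rates above agree. But the Kaplan-Meier curve and median would still be read as proportions of patients, and those are biased upwards and downwards respectively.

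Three stronger readings are tempting, and the documents do not support them.
- *That time to discharge is biased in the same way.* No such endpoint is named. A discharge rate would follow the binary method, and duration of hospitalization is assigned to no method.
- *That excess deaths can be hidden in this trial.* Death is in the primary composite, in mortality rate and survival time, and is the worst category of the ordinal scale. Only this one endpoint fails to show it.
- *That time to respiratory failure and time to ventilation must count death as an event.* Table 1 states the objective as "Clinical Severity: progression to severe respiratory failure/ICU admission or death", but the endpoint cell beside it lists time to respiratory failure, rate of ICU admission and rate of mortality as separate measures. Death is covered there. Folding it into the time endpoint is a choice of estimand, not the correction of an error.

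**Conclusion.** The point holds for time to reduction of supplemental oxygen. Followed as written, the protocol's methods and end of observation lead to deaths being censored in an endpoint that death makes impossible. Recovery is then overstated, and a difference in mortality leaves no trace in this comparison.

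Under the assumptions above, the overstatement at day 28 is about 3 points at 5% deaths, 7 at 10% and 18 at 25%. The direction does not depend on these assumptions. The size does: it rests on the assumed 10-day median, constant hazards and death rates, none of which the protocol supplies, and the upper end would need every primary failure expected in the control arm to be a death.

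Severity is low to moderate. This is one secondary endpoint in a trial that describes itself as exploratory phase II, and neither the primary analysis nor the reporting of deaths is affected.

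**What to change.** In section 10, Survival endpoints, add a rule for time to reduction of supplemental oxygen:
- estimate the cumulative incidence of oxygen reduction (Aalen-Johansen) with death as a competing event, and take the median from that curve;
- compare arms by a stratified Gray's test or a stratified subdistribution hazard ratio. Where status is known for everyone to the end of follow-up, this is equivalent to keeping deaths in the risk set as not recovered to day 28;
- show the cause-specific Cox hazard ratio beside it, so that the recovery rate among patients still at risk can also be read;
- state the horizon. The schedule of activities lists oxygen requirements up to the day-15 visit and mortality to day 28, so the rule should say which day applies.

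Keep Kaplan-Meier, log-rank and Cox for survival. Name the method for duration of hospitalization and, if it is analysed as time to discharge, handle death in the same way.

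The cost is protocol or SAP wording and standard procedures. Dates of death are already collected. The one small drawback is that a subdistribution hazard ratio is less familiar to readers, which the cause-specific ratio alongside it offsets.

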#### *General strategy for the rest of variables*

The rest of variables will be analysed according to the following strategy: The Fisher's exact test used for categorical variables, the t-test for Gaussian distributed variables and, for non-Gaussian continuous or ordinal variables, non-parametric methods (Mann-Whitney test).

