### ***Sample size estimation***

To obtain a power of 80.00% to detect differences in the contrast of the null hypothesis  $H_0: p_1 = p_2$  by means of a bilateral Chi square test for two independent samples, taking into account that the level of significance is 5.00%, and assuming that the proportion in the Reference group is 25.00%, the proportion in the Experimental group is 10.00%, and that the proportion of experimental units in the Reference group with respect to the total is 50.00 % it will be necessary to include 100 experimental units in the Reference group and 100 units in the Experimental group, totalling 200 experimental units in the study.

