## ***Randomisation Procedure***

Randomisation codes were produced by means of the PROC PLAN of the SAS system, with a 1:1 ratio of assignment between both arms, stratifying by centre, blocks multiple of 2 elements. The randomisation schedule will be managed from the eCRF in a concealed manner.

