### ***Primary endpoint***

The primary endpoint is the proportion of patients progressing to severe respiratory failure (Brescia-COVID  $\geq 2$ ), ICU admission, or death. The proportion of patients with failure at day 7, will be estimated using a log-binomial regression model including stratification variables. In the unexpected event that the model does not fit, the Poisson regression model with long-link and robust variance estimator will be used instead.

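### Shift outcomes and residual variables are compared with methods that ignore centre, although centre is the randomisation stratum; if centres differ in outcome, these tests are valid but conservative and give up a few points of power

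*Protocol*

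**What the plan says.** Protocol section 10, Randomisation Procedure, allocates 1:1, "stratifying by centre, blocks multiple of 2 elements". The primary endpoint is analysed with a "log-binomial regression model including stratification variables". Binary secondary and safety outcomes follow the same model. The mixed model for continuous outcomes also contains the stratification variables. For survival endpoints, the word stratified stands in brackets before both the log-rank test and the hazard ratio.

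Two classes have no stratum term. Under Shift outcomes, the estimate and 95% interval are the Hodges-Lehmann ones, described as the "median of all cross differences between treatments based on the Mann-Whitney distribution". Under General strategy for the rest of variables, Fisher's test is named for categorical variables, and then "the t-test for Gaussian distributed variables and, for non-Gaussian continuous or ordinal variables, non-parametric methods (Mann-Whitney test".

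Table 1 (Objectives and endpoints) lists measures such as "Oxygenation free days in the first 15 days" in its objectives column, with the matching count for ventilation and the duration of new oxygen and of new ventilation use.

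**The concern.** Blocking within centre balances the arms on anything that differs between hospitals. A comparison that leaves centre out still counts the between-centre variation as error, so its standard error is larger than the design warrants.

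Differences between hospitals are plausible here. Background care is given "according to each site local protocol", and oxygen weaning and discharge are decided locally. Day counts are the kind of outcome that such habits would move.

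At stake are efficiency and consistency: tests that run below 5%, intervals that are too wide, and secondary comparisons that do not follow the design as the primary one does.

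**Working it through.** **1. The plan's own figure.** The sample-size section states "To obtain a power of 80.00% to detect differences" "by means of a bilateral Chi square test for two independent samples", with 25% against 10% and a two-sided 5% level. With pooled variance:

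n = [1.96 √(2 × 0.175 × 0.825) + 0.8416 √(0.25 × 0.75 + 0.10 × 0.90)]² / 0.15² = (1.0532 + 0.4433)² / 0.0225 = 99.5, so 100 per arm.

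Power at 100 per arm is 80.2%. The figure reproduces, and the present point does not touch it.

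**2. Where centre enters.**

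| Class in section 10 | Centre in the stated method? |
|---|---|
| Primary endpoint | yes |
| Binary secondary and safety | yes, as primary |
| Continuous (mixed model) | yes |
| Survival | yes, in brackets |
| Shift (Hodges-Lehmann) | no |
| Rest (Fisher, t, Mann-Whitney) | no |

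**3. Which outcomes are exposed.**
- The day counts in Table 1 give one value per patient. They have no baseline and no repeated measurement, so the mixed model, with its baseline term and treatment-by-time interaction, does not fit them as written. They are neither binary nor time-to-event. The residual class is what remains.
- Duration of hospitalisation is assigned to no class. It could be continuous, survival or residual.
- The 7-point scale endpoint is a proportion of patients who worsen by at least a point. It is binary and already adjusted.

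**4. True size without centre.** Let r be the share of outcome variance between centres. The documents do not give r; 0 to 0.20 is assumed. With arms balanced within centre, the treatment difference varies only with the within-centre variance, but the unadjusted test divides by the total. Hence

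size = 2 [1 − Φ(1.96 / √(1 − r))].

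- r = 0: 5.0%
- r = 0.05: 4.4%
- r = 0.10: 1.96 / 0.9487 = 2.066, size 3.9%
- r = 0.20: 1.96 / 0.8944 = 2.191, size 2.8%

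The unadjusted interval is wider by 1 / √(1 − r): about 5% at r = 0.10 (1 / 0.9487 = 1.054) and 12% at r = 0.20 (1 / 0.8944 = 1.118). These are results for a t-type comparison and serve as a guide for the Hodges-Lehmann interval.

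**5. Power of the t-type test.** Take 100 per arm and an assumed effect of 0.4 of the total SD. The standard error is √(2/100) = 0.1414 and 0.4 / 0.1414 = 2.828. Unadjusted power is Φ((2.828 − 1.96) / √(1 − r)). Adjusted power is Φ(2.828 / √(1 − r) − 1.96).

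| r | Unadjusted | Centre-adjusted |
|---|---|---|
| 0 | 80.7% | 80.7% |
| 0.05 | 81.4% | 82.7% |
| 0.10 | 82.0% | 84.6% |
| 0.20 | 83.4% | 88.5% |

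**6. Rank tests, by simulation.** Assumed: 200 patients, equal centres, 1:1 within centre, skewed integer day counts, standardised effect 0.405. Entries are power of Mann-Whitney v centre-aligned ranks. Run A had 1,500 trials per cell and run B 3,000; Monte Carlo error is about 1 point in run A.

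| r | Centres | Run A | Run B |
|---|---|---|---|
| 0 | 8 | 78.2 v 78.0 | 78.8 v 77.9 |
| 0 | 20 | 79.6 v 80.3 | 78.4 v 77.0 |
| 0.10 | 8 | 80.7 v 83.8 | 77.7 v 79.4 |
| 0.10 | 20 | 81.7 v 83.7 | 79.8 v 80.8 |
| 0.20 | 8 | 82.6 v 87.1 | 80.1 v 83.1 |
| 0.20 | 20 | 81.7 v 86.3 | 81.9 v 85.6 |

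In run B, Mann-Whitney size was 3.6% and 3.8% at r = 0.10 (8 and 20 centres) and 3.0% and 2.9% at r = 0.20. Aligned ranks had 4.5% and 4.7% at r = 0.20. A further run gave smaller gains (0 to 1 point at r = 0.10, 2 to 4 at 0.20) and a cost of 0 to 2 points at r = 0, the 2 with 15 unequal centres.

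Van Elteren behaves differently. With normal data, an effect of 0.4 SD and 3,000 runs per cell, Mann-Whitney v van Elteren was:

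| r | 5 centres | 20 centres |
|---|---|---|
| 0 | 78.0 v 77.1 | 78.7 v 74.5 |
| 0.05 | 78.6 v 78.7 | 78.0 v 75.3 |
| 0.10 | 81.4 v 82.6 | 78.9 v 78.6 |
| 0.20 | 83.3 v 86.7 | 81.6 v 83.8 |

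**The case against.** The strongest reply is that this is detail for the SAP. Section 10 calls itself a summary and announces a detailed SAP, the main analyses already carry the strata, and nothing forbids running the residual tests by stratum. That holds for how small centres are handled. It does not fully answer the point, because the Protocol names the tests for these classes and they depart from its own practice elsewhere.

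Second, the list of exposed outcomes is partly inference, and this stands. The day counts appear only in the objectives column of Table 1; the endpoints beside them include times to event, which go to the survival methods. The endpoint lists in the synopsis and section 8 omit the counts. The Protocol does not say what counts as a shift outcome.

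A reader might infer three stronger things that the text does not support:
- That the ordinal scale is tested by an unstratified Mann-Whitney. The listed endpoint is dichotomised and adjusted.
- That Fisher's test brings the same problem to binary outcomes. Those go to the primary model; Fisher is left for residual categorical variables, and its own conservatism comes from discreteness.
- That power is lost in any event. It is lost only if centres differ, and with many small centres van Elteren can do worse than the unstratified test.

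Finally, this is an exploratory phase II trial with no stated power target for secondary outcomes. That limits the importance of the point, but not its correctness.

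**Conclusion.** The point holds as a minor inconsistency with a small, conditional cost. If 10% of outcome variance lies between centres, the unstratified tests run at about 3.9% and lose roughly 0 to 3 points of power; at 20%, about 2.8% and 2 to 5 points. If centres do not differ, there is nothing to gain, and an aligned rank test may cost about 0 to 2 points (van Elteren about 4 with 20 centres).

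These figures rest on assumptions that the documents do not supply: the between-centre share, the number of centres (5 to 20 tried), mostly equal centre sizes, and the effect size.

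Type I error is not inflated. The primary analysis, the adjusted binary outcomes and the 100 per arm are unaffected.

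**What to change.** For inferential comparisons under Shift outcomes and General strategy for the rest of variables:

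- Replace Mann-Whitney by a centre-aligned (or otherwise centre-adjusted) rank test, and compute the Hodges-Lehmann shift and its interval after centring within centre. Aligned ranks are preferable to van Elteren if many centres are small.
- Replace the t-test by a linear model with treatment and centre.
- Pool very small centres by a rule fixed before database lock.
- State which secondary outcomes fall under each method, including duration of hospitalisation and, if they are to be analysed, the Table 1 day counts.

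Replacing Fisher's test by Cochran-Mantel-Haenszel is not needed, because binary efficacy and safety outcomes are already adjusted.

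The cost is a few sentences in the Protocol or SAP and a few lines of code. Centre is already recorded as the randomisation stratum, so no new data are required. If the SAP already specifies centre-adjusted forms, only the Protocol wording needs to be aligned with it.
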